**Fig. 1 Fig1:**
[figure not shown]
Trial profile. Assessed for eligibility = Children aged 6 to 59 months who assessed for moderate acute malnutrition.. Randomized = Children aged 6 to 59 months who assessed for moderate acute malnutrition, fulfilled the inclusion criteria, recruited and randomly allocated. Loss to follow-up = Children who are randomly allocated to intervention and control groups and stop to participate in the study at any stage of the study. Discontinued = Children who are randomly allocated to intervention and control groups and discontinued from the study at any stage of the study. Analyzed at 12 weeks = Children aged 6 to 59 months whose information analyzed at 12 weeks

Allocation of participants to the intervention or control group will be done by one of the research team who has no information about the participant identity. After allocation into two groups, the subjects further categorized by the investigator into sub-groups, with equal numbers of children based on their location/neighborhood to assign one food distributor to each group in which food distributor can easily reach the households with the selected child.

### Blinding

Caregivers, data collectors and food distributers will be blinded for the intervention. Both supplements will be packed with similar packs, and will be distributed and prepared in the same way. The sugar which will be distributed for the intervention group will be mixed with the flour before packing. Vegetable oil will be distributed for both intervention and control groups with the supplement and food distributer will be assigned to help caregivers in cooking the porridge with 16 ml of oil for CSB+ group and with 8 ml of oil for intervention groups. The data will be analyzed by an individual other than the assessor.

### Data collection

Selected caregivers of children with MAM aged 6 to 59 months will be interviewed for collection of baseline data such as socio-demographic and economic status, dietary habits, child’s age, breastfeeding practices and history of child and maternal illness. The child’s weight will be noted using a seca weight scale to the nearest 0.1 kg. The data collectors will be sure that the scale is placed on a flat, hard, even surface and will weigh with minimal clothing.

Height will be recorded to the nearest 0.1 cm using a seca height scale for children aged 24 to 59 months. For children aged 6 to 23 months, length will be measured to the nearest 0.1 cm using a locally made wooden measuring board. Before starting height measurement, the data collectors will ensure that the height board is on level ground and the child is without shoes; the collector will kneel in order to get to the level of the child and will encourage the caregiver to help. For length, data collectors will measure the child lying down, being sure that the length board is placed on a flat and stable surface.

MUAC will be documented by non-stretchable standard United Nations Children’s Fund (UNICEF) plastic tape measures. The measurement will be taken half-way between the acromion and the olecranon processes, with the measuring tape fitting comfortably, but without making a depression in the upper arm. Weekly assessment of anthropometric measurement using MUAC will be done by the data collectors for intervention as well as control groups. On a monthly basis, data collectors will again collect anthropometrics using the MUAC, height or length board and weight scale which are identical equipment to that used at baseline. At the same time, they will observe for bilateral pitting edema. Based on the follow-up measurement of anthropometry children who developed sever acute malnutrition will be referred to SAM clinic.

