### Data analysis

All data collection sheets will be controlled by the field supervisors for completeness. EpiData version 3.1 will be used for all data entry. Two data clerks will enter data simultaneously to ensure data quality. Continuous data quality evaluation will be made through automatic consistency checks. Statistical significance is set at 5% for all analyses. Statistical analysis will be done using SPSS and STATA software for survival and hazard ratio. The probability of recovery rate will be predicted in Kaplan-Meier (log rank) curves of survival analysis. T-tests, analysis of variance (ANOVAs) and chi-square tests will be used to assess baseline characteristics. In accordance with recommendations for analyzing and reporting equivalence and non-inferiority trials, both intention-to-treat (ITT) and per protocol (PP) analyses will be done, and the 95% CI will be used to infer whichever variances are significant [24]. The ITT analyses will include all children enrolled in the study whereas the PP analyses will exclude children who lost to follow-up, refused and transferred out of the management programme but include children discharged as cured, died or non-cured.

Logistic regression will be used to test for interactions between the recovery rate and other variables. Mean recovery time and median recovery time, mean differences of MUAC and mean difference between WHZ scores will be computed to describe the magnitude of the difference between the two groups.

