### Outcome variables

The primary outcome measure of this study will be recovery rate. ‘Recovered’ will be defined as when a child attains a MUAC ≥12.5 cm and WHZ scores ≥ − 2, without bipedal edema. The secondary outcomes are the mean recovery time and average weight gain. Children who developed SAM during the study and/or persisted as moderately malnourished at the end of the 3-month follow-up will be considered to have failed the management for MAM.

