### Potential benefits

This project will be carried out in the kebeles (neighborhoods) found in Wolaita zone where there is no provision of a supplementary feeding program. The children participating in this study will get supplementary food for their malnutrition. The intervention will enhance recovery from MAM, and those recovered from MAM will be discharged and rejoin the community.

Children who may develop serious allergic reactions like difficulty in breathing, dizziness, weakness or any unusual signs will be referred for treatment. Such participants will be excluded from the trial. Children who are temporarily sick or do not feel well will be sent to the health facility for the treatment, and their measurements will be rescheduled for other days.

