## Discussion

MAM is a state that needs to be managed before it progresses to the life-threatening condition which is SAM. It is known that SAM has a high contribution to the global morbidity and mortality of young children [2]. Children with MAM need to achieve catch-up growth in weight and height, and they must be able to fight against infection and disease. That is why, currently, specific nutrient recommendations have recently been established for children with MAM living in developing countries [10].

The 2012 WHO technical note on supplementary foods for treating MAM in children aged 6 to 59 months recommends the delivery of locally available, nutritious foods to enhance nutritional status and prevent SAM [4]. It is important to evaluate the effect of feeding acute moderate malnourished children with local ingredient-based supplementary food. The food supplement referred in this paper is LIBS made from locally available ingredients either cultivated locally or found in the local market. If this study demonstrates positive results, it will provide a direction to the public, policymakers and academics, as locally available nutritious foods have the potential to enhance recovery from MAM and reduce the burden of malnutrition. The current study intends to determine the recovery rate from MAM by examining baseline and end-line measurements of MUAC and WHZ scores of the subjects. It will also evaluate the average weight gain and time of recovery.

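### Recovery is defined on MUAC, WHZ and edema, but only MUAC is taken weekly, so recovery time is interval-censored; the rule for a child who recovers and later relapses is also not fixed

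*Protocol article*

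**What the plan says.** Under Outcome variables, "The primary outcome measure of this study will be recovery rate", and recovered "will be defined as when a child attains a MUAC ≥12.5 cm and WHZ scores ≥ − 2, without bipedal edema". The same section names mean recovery time as a secondary outcome. It counts as failures the children who develop SAM during the study or are still moderately malnourished when the three months end.

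Under Data collection, "Weekly assessment of anthropometric measurement using MUAC will be done by the data collectors for intervention as well as control groups". Then: "On a monthly basis, data collectors will again collect anthropometrics using the MUAC, height or length board and weight scale". Edema is looked for at that same monthly contact. The article nowhere says that a weekly MUAC at or above the threshold prompts a weight and height measurement.

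Data analysis plans Kaplan-Meier curves with a log-rank test. It also lists "Mean recovery time and median recovery time" among the summaries of the difference between groups.

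The article describes the timing of recovery in two ways:
- **Attained during follow-up.** The Hypothesis refers to recovery within 12 weeks. The Abstract gives 12 weeks as a maximum for the intervention. The per-protocol definition in Data analysis speaks of children discharged as cured. Potential benefits says that "those recovered from MAM will be discharged and rejoin the community".
- **Status at the end.** The Discussion says the study will "determine the recovery rate from MAM by examining baseline and end-line measurements of MUAC and WHZ scores of the subjects". Description of interventions has the ration given daily for 12 weeks and mentions no earlier end.

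**The concern.** There are two separate problems.

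The first is measurement. At most weekly visits two of the three components of recovery are unknown, so the date on which a child met the full definition is known only to lie between two monthly visits. No later analysis document can repair this, because a WHZ that was not measured cannot be recovered. A named secondary outcome and the survival analysis depend on that date.

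The second is counting. The article does not say how to classify a child who meets the criteria at one visit and no longer meets them at the end, nor whether children discharged earlier are measured at end-line. If that choice is left until data are in hand, the primary proportion in each arm can be computed in more than one way. Whether the non-inferiority conclusion would change depends on whether such relapse differs between arms.

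**Working it through.** **1. Definition against schedule**

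| Component of recovery | Weekly visit | Monthly visit |
|---|---|---|
| MUAC ≥12.5 cm | yes | yes |
| WHZ ≥ −2 (weight and height or length) | no | yes |
| No edema | no | yes |

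Participant timeline ends follow-up within 11 weeks, with end-line data one week later. Taking a month as four weeks (an assumption), the full definition can be judged at about weeks 4, 8 and 12. That gives three possible event times.

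**2. Effect on recovery time**

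Inputs: 67% recovered by week 12 (control rate in Sample size calculation). A constant recovery hazard is assumed, because the article gives no time distribution.

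- Hazard: λ = −ln(1 − 0.67)/12 = 0.0924 per week; F(t) = 1 − exp(−λt).
- F(4) = 0.309, F(8) = 0.522, F(12) = 0.670, so first detection at weeks 4, 8 and 12 has probability 0.309, 0.214 and 0.148.
- Mean detected time among the recovered, monthly grid: (4 × 0.309 + 8 × 0.214 + 12 × 0.148)/0.67 = 7.0 weeks.
- Same formula on weeks 1 to 12: 5.4 weeks.
- Shift: 1.6 weeks. For 12-week rates from 60% to 76.8% it stays between 1.6 and 1.7 weeks.
- The median detected time is 8 weeks on both grids at a 67% rate. At 60% it moves from 10 to 12 weeks, and at 76.8% from 6 to 8.

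**3. Mean recovery time and the non-recovered**

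On the sample-size rates, 1 − 0.67 = 33% and 1 − 0.60 = 40% do not recover. They have no recovery time. A mean can be formed only among recovered children, which conditions on the outcome: an arm that brings slow children to recovery late would show a longer mean than an arm in which they never recover.

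A restricted mean to 12 weeks is defined for everyone. Under the model above it is 0.67 × 7.04 + 0.33 × 12 = 8.7 weeks on the monthly grid and 0.67 × 5.42 + 0.33 × 12 = 7.6 weeks on the weekly one. It solves the conditioning problem but not the grid problem.

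**4. A child who recovers and later relapses**

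Take a child who meets all criteria at week 4 and develops SAM at week 9. By the definition of recovery the child is recovered; by the failure rule in the same section the child has failed. A child who meets the criteria at week 4 and is moderately malnourished again at week 12 is a success if recovery is an event and a failure if it is end-line status.

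**5. What this could do to the comparison**

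The article gives no relapse rate, so the shares below are assumptions. If r is the share of recovered children who no longer meet the criteria at week 12, the end-line rate is (ever-recovered rate) × (1 − r).

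| Ever recovered, CSB+ / LIBS | r, CSB+ / LIBS | End-line rates, CSB+ / LIBS | Difference, ever → end-line |
|---|---|---|---|
| 67% / 67% | 10% / 10% | 60.3% / 60.3% | 0 → 0 |
| 67% / 60% | 10% / 10% | 60.3% / 54.0% | 7.0 → 6.3 points |
| 67% / 67% | 5% / 15% | 63.65% / 56.95% | 0 → 6.7 points |

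The non-inferiority margin is 7 points. Equal relapse barely moves the difference. Only relapse that differs by arm brings the two readings apart on the margin's scale.

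**The case against.** The best defence concerns the primary rate. A reader might infer that it has no single value, but the documents do not support that. The Hypothesis, the wording of the recovery definition, the per-protocol categories, the discharge statement and the Abstract's maximum duration mostly point to recovery attained within 12 weeks. A child discharged as recovered has not remained malnourished throughout. The end-line reading rests mainly on one Discussion sentence, and the next sentence there promises time of recovery, which two measurements cannot give. Nor does monthly spacing leave an end-line rate undefined, since WHZ is taken then. This stands. What remains is a conflict of wording and a missing counting rule, sharpest for the child who recovers and then develops SAM.

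A reader might also set a shift of 3.4 to 10.1 points (67% × 5% to 67% × 15%) against the 7-point margin. That shift is in one arm's rate, while the margin applies to the difference between arms, so the comparison is not valid without an assumption of differential relapse.

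On recovery time, Data analysis states no time grid, and the schedule is common to both arms, so a log-rank test on shared visit dates remains usable, with many ties. That too stands. It does not rescue the recovery-time estimates, which come out later and coarser than the weekly follow-up announced in the Abstract would suggest.

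Finally, the article does not say that SAM or death will be censored. SAM is already a failure and deaths stay in the per-protocol set, so there is no error of that kind to correct.

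**Conclusion.** The point holds in two parts of unequal strength.

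The mismatch between definition and schedule is certain from the text. The full definition can be judged at about three times, so recovery time and the survival analysis are interval-censored. Under a constant hazard with 67% recovered by week 12, the mean detected time is about 1.6 weeks later than with weekly checks. A mean recovery time that leaves out the expected 33–40% non-recovered is not a comparison of all randomised children.

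The second part is narrower. The article leans towards recovery attained within 12 weeks but contradicts this in places, and it does not say how a child who relapses is counted. The consequence for the between-arm difference cannot be derived from the article. It is near zero with equal relapse and 6.7 points under the assumed 5% against 15%. No threat to the non-inferiority conclusion is shown, only that the choice should not remain open. The point should be corrected, at little cost; it does not invalidate the design.

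**What to change.** - **Endpoint.** State one primary endpoint: all criteria met at a scheduled visit with full measurement, up to and including week 12. State how a child who later relapses or develops SAM is counted. Use week-12 status in all children as a sensitivity analysis. Cost: wording, plus an end-line measurement for any child discharged earlier, if one is not already intended.
- **Recovery time.** Choose one of two routes. Either keep the monthly grid and use discrete-time or interval-censored methods, which costs only wording. Or take weight, height or length and edema at the existing weekly visit when MUAC first reaches 12.5 cm, which adds one or a few short measurements per child with staff and equipment already in use.
- **Summary measure.** Replace the mean among recovered children by the restricted mean time to 12 weeks in all randomised children. Cost: wording.
- **Reconciliation.** The investigators must reconcile the statements on discharge, ration duration and end-line assessment in the Abstract, Description of interventions, Potential benefits and Discussion. If the extra weekly measurement is adopted, they must also say how it relates to discharge. No discharge or feeding rule is proposed here.

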## Background

Worldwide, acute malnutrition is a major contributor to deaths and disabilities in children, affecting about 51.5 million children below 5 years of age [1, 2]. Chronic food insecurity, poverty, poor feeding practice, limited household food availability and infections are considered possible reasons for developing acute malnutrition [3]. Acute malnutrition is associated with at least 12.6% child mortality, occurring among children aged below 5 years [2].

The Ethiopian Demographic and Health Survey of 2011 showed that about 10% of children aged below 5 years had acute malnutrition, and among these, 70% had MAM, defined by weight-for-height z-score (WHZ) between − 3 to − 2 Standard Deviations and/or mid-upper arm circumference (MUAC) of between ≥11.5 cm and < 12.5 cm, without bilateral pitting edema [4, 5]. Most malnutrition-related deaths occur in mildly or moderately malnourished children. In low- and middle-income countries, acute malnutrition is associated with about one in six deaths. Of these, 10.2% are due to MAM [6]. The death risk among moderately malnourished children is three-fold compared with that of non-malnourished children [1].

Children with MAM are susceptible to develop severe acute malnutrition (SAM) if they are not managed adequately. It is known that SAM has a high contribution to the global morbidity and mortality of young children. Therefore, children with MAM need to be treated with adequate nutrient-dense foods to prevent progressing to the life-threatening condition [2, 4].

In Ethiopia, the existing strategy for the management of MAM is a supplementary feeding program; however, this is restricted to districts where chronic food insecurity is present. In the areas not determined to be chronically food insecure, there are no food supplementation programs for MAM children. In these districts, the strategy to manage MAM children includes vitamin A supplementation, deworming and dietary counseling provided to the families [2]. The dietary counseling is provided to the families in these districts on the understanding that they have access to all foods required for child feeding, but lack knowledge on how best to use them [7].

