### Setting

This study will be conducted in Damot Pulassa district located in Wolaita zone. Like other districts of Wolaita, this district has the highest population densities of more than 700 persons per square kilometer [20]. The district characterized by having a fragmented farm and land ownership. The disparity between land and population balance has by far persisted the main contributing factor for the occurrence of endemic food insecurity [21]. Damot Pulassa district is classified as a maize and root crop livelihood zone because such crops are the main ones produced in the area. The district is serving by five health centers and 23 health posts. These health posts are led by health extension workers and deliver nutrition-linked services like nutrition education, screening for nutritional status of young children and nutritional management of the malnourished ones. The district was selected based on a consideration of the high level of food insecurity, high level of child malnutrition, good geographical location and access to transportation.

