### Exclusion criteria

Children with SAM based on WHO 2009 child growth standards and/or children with bilateral pitting edema [22].Children with any illness or other medical complications that prevent them from safely consuming supplementary food.Children already participating in other interventions.

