### Participant timeline

Children aged 6 to 59 months will be assessed for MAM based on inclusion and exclusion criteria using MUAC and weight-for-height/length z-scores. The screening procedure will end within 3 weeks. Consenting of the eligible respondents (mothers of children aged 6 to 59 months) and randomization of the eligible subjects will take place 1 week after screening completed during which the subjects will be allocated into intervention and control groups, along with baseline data collection. Follow-up interviews with the anthropometric assessment will be done weekly and monthly basis after the allocation date and completed within 11 weeks. End-line data collection will take place 1 week after ending a follow-up interview (Fig. 2).

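### Bilateral pitting oedema is checked only monthly in follow-up although data collectors see every child weekly; moving the check to the weekly visit cuts the longest scheduled wait from about 4 weeks to 1

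*Protocol article*

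**What the plan says.** The Data collection section of the protocol article sets two follow-up rhythms. The weekly one is MUAC only: "Weekly assessment of anthropometric measurement using MUAC will be done by the data collectors for intervention as well as control groups". The monthly one repeats MUAC and adds weight and height or length. The oedema check comes directly after the monthly measurement: "At the same time, they will observe for bilateral pitting edema". The section closes with the referral rule: "Based on the follow-up measurement of anthropometry children who developed sever acute malnutrition will be referred to SAM clinic".

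Participant timeline repeats the two rhythms without mentioning oedema: "Follow-up interviews with the anthropometric assessment will be done weekly and monthly basis after the allocation date and completed within 11 weeks". End-line data are collected one week after that, at week 12.

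Oedema has a role of its own, separate from MUAC and WHZ, at three points:

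- Background defines MAM as "without bilateral pitting edema".
- Exclusion criteria remove "Children with SAM based on WHO 2009 child growth standards and/or children with bilateral pitting edema".
- Outcome variables counts a child as recovered only if "without bipedal edema".

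**The concern.** Oedema is a sign that a MUAC tape does not detect. A child can develop it while MUAC remains at 11.5 cm or more, and the weekly visit as described would then raise no flag. Such a child has left the condition the trial is meant to treat, yet under the stated schedule may stay on the supplement until the next monthly visit before anyone is due to look for the sign.

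The referral rule adds to this. It rests on follow-up anthropometry and does not name oedema as a trigger.

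What is at stake is the child's safety and the timing of referral. The point does not concern the 12-week recovery proportion or bias between the arms, since the schedule is the same in both. Nor is it a contradiction between sections: the schedule is clear, but it puts this check on the slower of two existing visits.

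**Working it through.** The article gives no figure for detection delay, so there is none to reproduce. The calculation compares the stated schedule with a weekly one.

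**Inputs**

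- Weekly MUAC contact in both arms; monthly full measurement with the oedema check (Data collection).
- Follow-up visits within 11 weeks and end-line one week later, so 12 weeks or 84 days. End-line is taken as a check (Participant timeline).
- Assumption: onset of oedema is equally likely on any day of the 84. The maxima do not need this assumption; the means and proportions do.

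**Formulas.** For checks T days apart, the maximum wait is T, the mean wait is T/2, and P(wait > w) = (T − w)/T. For unequal intervals T1, T2, … that sum to 84, the mean is ΣTi²/(2 × 84).

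**Stated schedule, monthly read as 4 weeks (days 28, 56, 84)**

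- Maximum 28 days; mean 28/2 = 14 days.
- P(wait > 7) = 21/28 = 0.75; P(wait > 14) = 14/28 = 0.50; P(wait > 21) = 7/28 = 0.25.

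**Stated schedule, monthly read as 30 days (days 30, 60 and end-line 84)**

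- Maximum 30 days; mean (30² + 30² + 24²)/168 = 2376/168 = 14.1 days.
- P(wait > 7) = (23 + 23 + 17)/84 = 0.75; P(wait > 14) = (16 + 16 + 10)/84 = 0.50.

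**Weekly schedule**

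- Maximum 7 days; mean 7/2 = 3.5 days.

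Simulating uniform onsets over 12 weeks gave the same results: mean 2.00 weeks with 4-weekly checks and 0.50 weeks with weekly checks.

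**Gain per case:** 14 − 3.5 = 10.5 days on average.

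**Allowing for other contacts.** Suppose a share m of cases is found at once by some other route under either schedule. The article gives no value for m, so a range is shown. The mean gain is 10.5 × (1 − m):

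| m (assumed) | Mean gain, days |
|---|---|
| 0 | 10.5 |
| 25% | 7.9 |
| 50% | 5.3 |
| 75% | 2.6 |

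**Is the check scheduled anywhere else in follow-up?**

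- Recruitment covers oedema at screening only.
- Description of interventions has food distributors in the home daily, for cooking, feeding and recording intake.
- Data quality management has supervisors and the investigator visit to check feeding.
- Setting describes general health-post services, including "screening for nutritional status of young children and nutritional management of the malnourished ones".
- Potential benefits sends sick children, and those with allergic reactions or unusual signs, for treatment.

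Any of these could lead to oedema being noticed. None is described as an oedema check.

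**The case against.** The strongest reply is that nothing here is wrong. A monthly check breaches no standard set in the article, and more frequent monitoring can be proposed for almost any trial. The article is also a condensed account. The contents of the weekly form are not shown, and data collectors are not told to ignore swelling they happen to see.

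The computed wait is moreover for the scheduled check and need not be the child's actual wait. Someone from the trial is in the home every day, and the provision for unusual signs is wide enough to cover visible swelling. No rate of new oedema is given, so the yield is unknown and could be very small. The uniform-onset means also leave out that recovered children are discharged. Finally, SAM by WHZ would still be looked for only monthly.

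Much of this stands. The actual delay is unknown, the number of cases is unknown, the fix leaves WHZ untouched, and there is no inferential consequence. These limits keep the point at the level of an optional improvement.

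Two parts do not stand. First, the timing was not left out by condensation: the article states it and ties the check to the monthly visit, and an unseen form does not override that. Second, daily contact for cooking and feeding is no substitute for an assigned check, because nobody at those visits is told to look for oedema or record it.

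**Conclusion.** The concern holds as a low-cost safety improvement. On the stated schedule, a child whose only new sign is oedema may wait up to about 4 weeks for a scheduled check, on average about 2. A weekly check brings this to at most 1 week, on average half a week. The means rest on uniform onset over 84 days and on end-line counting as a check; reading monthly as 30 days instead of 28 hardly changes them.

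The mean gain of 10.5 days per case is an upper figure that assumes no other contact finds the oedema first; it falls to 2.6 days if three quarters of cases are found at once by other routes. The total benefit cannot be stated, because the article gives no incidence of oedema during treatment. No effect on the non-inferiority conclusion is claimed.

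**What to change.** In Data collection, move the bilateral pitting oedema check to the weekly MUAC visit in both arms, record the result each week, and name oedema in the referral rule so that any child who has it goes to the SAM clinic at once, whatever the MUAC.

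The cost is one more item on the weekly form. The same data collectors already see each child weekly and already do this check monthly, so no extra visit, staff or equipment is needed. The possible downside is a few more, or earlier, recorded failures due to SAM. Detection of SAM by WHZ stays monthly, because it needs the scale and the height or length board.
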